## 7.2 Group Allocation

Randomization will be conducted in a 1:1 ratio at the level of the team and stratified by study site using an online random number generator. Randomization will be conducted in blocks of two to ensure equal distribution of teams across study arms. Study packages will be prepared with opaque envelopes to achieve allocation concealment. Sequentially numbered recruitment packages provided for each site will contain unique identifier codes for participants, along with study arm assignments. Personnel who enroll participants and those who assign participants to interventions will have no advance access to the sequence. On the trial day, the principal investigators or delegated investigators will obtain written informed consent from participants before any study procedures, and selection criteria will be checked prior to participation in the study. Immediately after written consent, the authorized staff will access only the assignment function to obtain the participant's allocation. Assignment will occur once per participant, with audit trails documenting day and time.

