## 2.4 Trial Design and Setting

We plan to conduct an open-label, prospective, simulation-based, multicenter, cluster randomized clinical trial at both Geneva (Switzerland) and Calgary (Canada) Children's Hospitals. Simulation-based research confers the advantage of answering research questions without risk of harm to patients. The scenarios will be conducted in situ at the institutional simulation centers. We will compare team performance using the InterFACE-AR supportive tool (intervention) or conventional AHA PALS pocket reference cards (control) during standardized pediatric IHCA. Participants will be recruited to the study in teams of three, comprised of a team leader, charting nurse, and medication nurse. Additionally, four trained research actors will fill the scripted roles of CPR provider / CPR Coach (2

actors, alternating roles), an airway provider, and a Bedside Provider to make a resuscitation team of 7 providers. The actor will be trained with methodology successfully used in prior multicenter trials. Participant teams will manage one CA simulation scenario (see below), using the specific trial intervention assigned during randomization. No changes will be made to the apps and devices during the study. **Figure 2** shows the trial flow chart and **Figure 3** the trial checklist. As this simulation-based study enrolls only healthcare professionals, there will be no patient or public involvement in the design, conduct, or reporting of the trial. The trial will be conducted according to appropriate guidelines and follow the 2025 Consolidated Standards of Reporting Trials (CONSORT) reporting guideline. The present trial protocol adheres to the SPIRIT 2025 checklist (see **Appendix** at the end of the protocol). It is our intention to present the results at scientific congresses and to publish the results in a peer-reviewed journal, irrespective of the magnitude or direction of effect.

[figure not shown]

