## **2.6 Recruitment Process**

To ensure sufficient subject enrolment for reaching the target sample size on the day of participation, teams will be randomly recruited and scheduled weeks prior to the study commencement by a blinded non-investigator. To mitigate preparation bias, they will be informed about the upcoming simulation study without knowledge of its objectives and outcomes. In cases of participant unavailability, the research team will arrange for a replacement.

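### Fixed, published blocks of two within site reveal the arm of the second team in each pair (8 or 9 of 18 teams), leaving replacements and day-of changes open to selection

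*Combined protocol and SAP*

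**What the plan says.** Section 7.2 sets the unit and strata: randomisation is "at the level of the team and stratified by study site using an online random number generator". It then fixes the block size: "Randomization will be conducted in blocks of two to ensure equal distribution of teams across study arms". Each site works through its own sequence: "Sequentially numbered recruitment packages provided for each site will contain unique identifier codes for participants, along with study arm assignments". Concealment rests on envelopes ("Study packages will be prepared with opaque envelopes to achieve allocation concealment"), on staff having no prior sight of the sequence, and on opening the allocation only after written consent. Section 7.2 also has selection criteria checked on the trial day.

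Section 2.4 gives the setting, "at both Geneva (Switzerland) and Calgary (Canada) Children's Hospitals", and calls the trial open-label.

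Section 2.6 contains the main safeguard: teams are recruited at random and booked weeks ahead by a blinded person who is not an investigator. It then adds: "In cases of participant unavailability, the research team will arrange for a replacement". Section 6.2 allows short rescheduling windows on the day. Section 2.5 excludes anyone who cannot carry out the tasks of their role. Section 9.4 keeps in reserve a shift of recruitment between sites. Section 7.1 plans 18 teams, 9 per arm. The number of teams per site is not given.

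**The concern.** Concealment means that nobody who can influence which team comes next can know its arm. With one published block size of two, a separate sequence per site and past arms in plain view, the second arm of each pair follows from the first. No envelope needs to be opened. The SPIRIT checklist reproduced in the protocol (item 21b) says that blocking details belong in a document unavailable to enrolling or assigning staff; here the block size is printed in section 7.2.

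If a replacement, a change of order or an eligibility judgement is made with the arm known, stronger or weaker participants can end up in one arm. With 9 teams per arm, one or two such choices carry weight. The primary comparison in section 7.4.2 is an unadjusted difference, so the planned analysis would not correct for it.

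**Working it through.** **Inputs.** Block size 2, 1:1 ratio, team as unit, separate sequence per site (7.2); two sites and open label (2.4); 18 teams, 9 per arm, SD 25.2 s (7.1). Teams per site are assumed: 10+8, 12+6 and 9+9. The documents give no figure for predictability. Their one figure to reproduce is the equal split.

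**1. Does the plan give 9:9?** With even site totals every block is completed, so each site is balanced and the trial ends 9:9. With 9+9, each site ends on a half-filled block at 5:4. The two sites lean the same way with probability 1/2, so the trial ends 10:8 with probability 1/2.

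**2. Allocations known for certain under blocks of two.** One per completed block.
- 10+8: 5 + 4 = 9 of 18 (50%). 12+6: 6 + 3 = 9 of 18 (50%).
- 9+9: 4 + 4 = 8 of 18 (44%).

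**3. Correct best guesses under blocks of two.** The first of a pair is guessed with probability 1/2, the second with probability 1.
- Even totals: 9 × 0.5 + 9 = 13.5 of 18 (75%).
- 9+9: 10 × 0.5 + 8 = 13 of 18 (72%).

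**4. Alternative: one permuted list per site.** For a list of 2m teams with m per arm, the expected number known for certain is 2m/(m+1). The expected number of correct best guesses is m + (4^m / C(2m,m) − 1)/2.

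| List length | Known for certain | Share | Correct guesses | Share |
|---|---|---|---|---|
| 2 | 1.00 | 50% | 1.50 | 75% |
| 4 | 1.33 | 33% | 2.83 | 71% |
| 8 | 1.60 | 20% | 5.33 | 67% |
| 10 | 1.67 | 17% | 6.53 | 65% |

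Lists of 10 and 8 together: 1.67 + 1.60 = about 3.3 of 18 known for certain, and 6.53 + 5.33 = 11.86 of 18 (66%) guessed correctly.

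**5. Alternative: random blocks of 2, 4 and 6.** Sizes are equally likely, and the observer knows the set of sizes but not the ones drawn. By exact enumeration, about 0.5 to 0.6 of 18 allocations are known for certain (3%), and 67–69% are guessed correctly. Exact 9:9 is missed in about 34% of completed 10+8 trials: about 32% end 10:8 and 2% end 11:7. With 9+9 it is missed in about 52%, against 50% for blocks of two.

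**6. What one or two steered teams could do (illustration).** The SE of the difference is 25.2 × √(2/9) = 11.9 s. Suppose there is no true effect, and two teams in one arm are each 1 SD faster through selection. The shift is 2 × 25.2/9 = 5.6 s, and the two-sided type I error rises from 5% to 7–8%. If two teams in the other arm are also 1 SD slower, the shift is 11.2 s and the error 14–16%. The ranges cover the t and normal calculations. The 1 SD figure is an assumption and does not come from the documents.

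**The case against.** The strongest reply is section 2.6. Teams are drawn at random and scheduled weeks ahead by someone blinded, so initial composition and order are set before any arm is visible. Knowing an arm does harm only if somebody can then change who attends. This stands, and it confines the exposure to exceptions: a replacement, a same-day change or a trial-day eligibility judgement. It does not remove the exposure. Replacements belong to the research team and no blinding is stated for that step.

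A reader might infer more than the documents support:
- *That concealment fails for the whole trial.* It fails for the second team of each completed pair. The first stays concealed.
- *That the research team also controls same-day rescheduling.* Section 6.2 names no one and does not say that teams may swap order. It is only a step without a stated rule.
- *That the result will be biased.* Step 6 shows what selection could do. Nothing in the documents indicates that it will happen.
- *That individuals are randomised, because section 7.2 says* "Assignment will occur once per participant, with audit trails documenting day and time". The same section places randomisation at team level. This is loose drafting, as is describing both site envelopes and an assignment function while the Summary calls randomisation centralised. Neither bears on predictability.

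It is also fair to say that blocks of two were chosen for balance, that part of the remedy (allocation after consent, with an audit trail) is already planned, and that best-guess success falls only from 75% to about 66% with the permuted lists. The gain lies mainly in the allocations known for certain, which fall from 9 to about 3.3.

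**Conclusion.** The concern holds in a limited form. Under the stated rule, 9 of 18 allocations (even site totals) or 8 of 18 (9+9) are known once the preceding team has run, and the concealment measures in section 7.2 cannot prevent this. The count rests on an assumed site split and on staff seeing past arms at their own site, which the open-label design implies. Scope for selection is narrowed by section 2.6 to replacements, same-day rescheduling and trial-day eligibility checks. Blocks of two also fail to secure 9 per arm if both sites run an odd number of teams. This is a design choice that should be changed because prevention is cheap; it is not evidence that the comparison is invalid.

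**What to change.** In section 7.2, replace blocks of two with one permuted 1:1 list per site over an even planned number of teams (for example 10 and 8), generated and held centrally. State the planned number per site. Release the arm once per team, after all three members have consented, and allow replacements or changes of order only before that release. Align the envelope, assignment-function and per-participant wording with this single procedure.

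Cost: a new list before enrolment and a paragraph edit. The downside is possible small imbalance if a site stops before its list is complete or recruitment is moved between sites (section 9.4). For example, a list of 8 stopped at 6 misses 3:3 with probability 1 − C(4,3)²/C(8,6) = 1 − 16/28 = 43%.

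Randomly varying blocks of 2, 4 and 6, with sizes kept from the sites, are an alternative. They leave only about 3% of allocations certain, but miss exact 9:9 in about 34% of completed 10+8 trials, almost always at 10:8. The choice is between guaranteed balance on completion and lower predictability; either improves concealment over the present rule.

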## 7.3 Blinding

Due to the nature of the intervention, blinding of reviewers to group allocation will not be feasible. Post-scenario video review will be done independently by two trained raters. In the case of disagreement, a third independent evaluator will help reach a consensus. An intraclass correlation coefficient will be computed. The investigators will remain unaware of the outcomes until all data are unlocked for analysis at the end of the trial.

## 7.4 Statistical Analysis Plan

### 7.4.1 Data Summary

We will summarize the demographic characteristics of participants in both the InterFACE-AR group and the PALS pocket card group. For numeric variables (e.g., height), the mean and standard deviation will be reported. For categorical variables (e.g., sex, profession), counts and percentages will be presented. A template for the demographic summary table is provided below.

| Characteristics | Participants a |                               |
|-----------------|---------------------------|-------------------------------|
|                 | InterFACE-AR
(n = 27)  | PALS pocket cards
(n = 27) |
| Sex             |                           |                               |
| Male            | X (X%)                    | X (X%)                        |
| Female          | X (X%)                    | X (X%)                        |
| Height (SD), cm | Mean (SD)                 | Mean (SD)                     |
| Profession      |                           |                               |

|                                                    |           |           |
|----------------------------------------------------|-----------|-----------|
| Attending physician                                | X (X%)    | X (X%)    |
| Resident / Fellow                                  | X (X%)    | X (X%)    |
| Physician assistant                                | X (X%)    | X (X%)    |
| Nurse                                              | X (X%)    | X (X%)    |
| Nurse Practitioner                                 | X (X%)    | X (X%)    |
| Resuscitation training (BLS/ACLS/PALS/PEARS)       |           |           |
| Instructor status                                  | X (X%)    | X (X%)    |
| < 1                                                | X (X%)    | X (X%)    |
| 1 - 6                                              | X (X%)    | X (X%)    |
| 7 - 12                                             | X (X%)    | X (X%)    |
| > 12                                               | X (X%)    | X (X%)    |
| Resuscitation events involved in, n (SD)           | Mean (SD) | Mean (SD) |
| Simulated resuscitation events involved in, n (SD) | Mean (SD) | Mean (SD) |
| Real CPR in the past year, n (SD)                  | Mean (SD) | Mean (SD) |
| Simulated CPR in the past year, n (SD)             | Mean (SD) | Mean (SD) |
| Experience of headset with immersive technology    |           |           |
| Never                                              | X (X%)    | X (X%)    |
| Once a month or less                               | X (X%)    | X (X%)    |
| Once a week to once a month                        | X (X%)    | X (X%)    |
| Experience of using AR for education               |           |           |
| Never                                              | X (X%)    | X (X%)    |
| Once a month or less                               | X (X%)    | X (X%)    |
| Once a week to once a month                        | X (X%)    | X (X%)    |

422

#### 423 **7.4.2 Primary Outcome - Time to administer 1st dose of epinephrine**

424 Due to the small sample size, non-parametric approaches will be used to account for potential violations  
425 of assumptions underlying parametric tests. Boxplots will be generated to assess the distribution of data  
426 in both study arms. If the data are approximately symmetric and normally distributed, the mean  
427 difference will be estimated; if the data are skewed or non-normally distributed, the median difference  
428 will be estimated instead. Bootstrapping with 10,000 resamples will be used to calculate 95% confidence  
429 intervals for the estimated differences. Permutation tests with 10,000 iterations will be conducted to  
430 determine 2-sided p-values.

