## **7. Statistical considerations**

### **7.1 Power and Sample Size Calculation**

The calculation is based on the primary outcome, time to first epinephrine dose. Prior data report a median of approximately 165 seconds (IQR of 139 to 173 seconds). Using the Greco et al. approach, and using the 1st and 3rd quartiles, we estimate SD as  $(173-139)/1.35 = 25.2$  seconds. With a two-sided

$\alpha=.05$  and 90% power to detect a clinically meaningful absolute reduction of 35 seconds, and assuming similar variability between groups, 18 teams (9 per arm) are required.

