#### 431 **7.4.3 Secondary Outcomes – Time to other critical tasks during cardiac arrest management**

432 These outcomes include time to initiate CPR, time to first dose of defibrillation, time to establish  
433 advanced airway, time to 1st and 2nd drugs to treat hyperkalemia, chest compression fraction and peri-  
434 shock durations. Time to these critical tasks and BLS outcomes (e.g., chest compression fraction, peri-  
435 shock pause durations) will be analyzed using the same non-parametric approaches applied to the  
436 primary outcomes. After assessing the data distribution, bootstrapping and permutation tests with 10,000

iterations will be used to estimate 95% confidence intervals and p-values for the differences. A template table is presented below.

| Variables | InterFACE-AR
(n = 9) | PALS cards
(n = 9) | Median/mean
Difference
(95% CI)* | P
value** |
|-----------|-------------------------|-----------------------|----------------------------------------|--------------|
| Outcome 1 | X (X – X)               | X (X – X)             | X (X, X)                               | X            |
| Outcome 2 | X (X – X)               | X (X – X)             | X (X, X)                               | X            |
| ...       | X (X – X)               | X (X – X)             | X (X, X)                               | X            |

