#### **7.4.6 Secondary outcomes - UEQ and TAM (for intervention group only)**

The User Experience Questionnaire (UEQ) and the Technology Acceptance Model (TAM) survey will be administered to participants in the InterFACE-AR group only. Rather than presenting data for each individual item, we will report the statistical summaries (mean and standard deviation) for each construct within both tools. The UEQ includes six constructs: attractiveness, perspicuity, efficiency, dependability, stimulation, and novelty. The TAM includes two constructs: perceived usefulness and perceived ease of use. For each construct, the mean and standard deviation will be reported, and Cronbach's alpha will be calculated to assess the internal consistency of the items within each construct.

In the case of missing data, a complete case analysis will be conducted. No multiple imputations are planned. All statistical tests will be two-sided with a type one error risk of 5%. All statistical analyses will be performed with R software (version 4.5.0; Foundation for Statistical Computing).

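### Section 7.4.2 lets a visual reading of outcome boxplots choose between a mean and a median difference, and names no permutation statistic, so the primary result is not fixed before outcomes are seen

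*Combined protocol and SAP*

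**What the plan says.** Section 7.4.2 starts the primary analysis with a look at the outcome: "Boxplots will be generated to assess the distribution of data" in each study arm. If the data appear symmetric and close to normal, the mean "difference will be estimated; if the data are skewed or non-normally distributed, the median difference" takes its place. Bootstrap intervals and two-sided permutation p-values follow, with 10,000 resamples or iterations each. The text does not say which quantity is permuted.

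Section 7.4.3 carries this over to the secondary times, chest compression fraction and peri-shock pauses: "After assessing the data distribution, bootstrapping and permutation tests with 10,000" iterations are used, and the template table has a combined median/mean column.

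Three other places bear on the choice without settling it.
- Section 4 defines the primary outcome as an interval in seconds but gives no group summary. The SPIRIT checklist nevertheless points to that page for item 16, which asks for the method of aggregation. Item 27d, on sensitivity analyses, is marked not applicable.
- Section 7.3 keeps investigators unaware of outcomes until the data are unlocked for analysis.
- Section 7.1 sizes the trial from an SD and an absolute difference: "and 90% power to detect a clinically meaningful absolute reduction of 35 seconds", "assuming similar variability between groups".

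**The concern.** A primary analysis should be settled before anyone can see which version favours the intervention. Here the deciding step is a judgement by eye on plots of the outcome by arm, and such plots display the treatment effect along with the shape. The protection in section 7.3 ends at the point when these boxplots are drawn.

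Nine values per arm say little about shape, and the plan has no rule for arms that look different from each other. The two summaries also answer different questions if the system changes the spread or tail of the times as well as their centre. For example, it might help only the slowest teams.

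Because the permutation statistic is unnamed, the p-value may or may not test the quantity that is reported. At stake are the credibility of the primary p-value and, in some circumstances, power.

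**Working it through.** **Inputs.** Two-sided α = 0.05 (sections 7.1 and 7.4.6), difference 35 s, 9 teams per arm, and SD = (173 − 139)/1.35 = 25.2 s (section 7.1). The source is given as: "Prior data report a median of approximately 165 seconds (IQR of 139 to 173 seconds"). The median lies 165 − 139 = 26 s above the lower quartile and 173 − 165 = 8 s below the upper, so the plan's own prior data are asymmetric.

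**The plan's figure.** n per arm = 2(z₁₋α/₂ + z₁₋β)²(SD/Δ)² = 2(1.960 + 1.282)²(25.2/35)² = 10.9, so 11 per arm; the t-test version gives 12. The stated 9 per arm is not reproduced. At 9 per arm the standard error is 25.2 × √(2/9) = 11.88 s and 35/11.88 = 2.946. Normal-approximation power is then Φ(2.946 − 1.960) = 83.8%, and t-test power is 79.0%. That shortfall is a separate matter. It is shown here because about 79% is the baseline for what follows.

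**Simulation.** Nine per arm, a pure 35 s shift, two-sided permutation test at 5%, with either the difference in means or the difference in medians as the statistic. The normal row uses 6,000 trials and the two-piece row 3,000, each with 10,000 permutations. The other rows use 6,000 trials and 2,000 permutations. Normal, lognormal and t data have SD 25.2 s. The two-piece normal is matched to the cited quartiles, with half-SDs 26/0.6745 = 38.5 s and 8/0.6745 = 11.9 s.

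| Shape | Power, mean | Power, median | Verdicts disagree |
|---|---|---|---|
| Normal | 78.5% | 66.9% | 15.8% |
| Two-piece, cited quartiles | 74.6% | 74.4% | 16.8% |
| Lognormal, log-SD 0.5 | 80.8% | 83.2% | 14.1% |
| Lognormal, log-SD 1 | 85.8% | 96.0% | 13.8% |
| t, 3 df | 86.2% | 85.7% | 12.0% |

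The loss with normal data is 78.5 − 66.9 = 11.6 points (95% Monte Carlo interval 10.7 to 12.6).

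**If a rule triggers the switch (normal data).**
- Shapiro-Wilk p < 0.05 in either arm moves about 9% of datasets to the median. Power is 77.8% against 78.6% for always using the mean in the same run, a loss of just under 1 point.
- A boxplot outlier in either arm occurs in about 51–52% of truly normal datasets. Power is 72.6%, a loss of 78.6 − 72.6 = 6.0 points.
- A repeat with 4,000 trials gave 79.1% (mean), 78.2% (Shapiro) and 72.5% (outlier): losses of 0.9 and 6.6 points.

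**Type I error.**
- Keeping the smaller of the two p-values, normal data: 6.1% and 6.9% in two runs.
- Shapiro rule 5.4%, outlier rule 4.9%, normal data. The repeat gave 4.6–5.1% (normal) and 4.3–5.1% (two-piece).
- With lognormal and t data, the two rules gave 4.2–5.6%.

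**The case against.** The strongest reply is that section 7.4.2 ties the choice to shape and not to p-values, and that a shape-based choice does little harm. This stands. Simulated shape rules keep the error rate near 5%. With the two-piece shape they gave 76.0–76.3% power, against 75.3% for always using the mean.

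A reader might go further than the documents allow in five ways.
- **That the plan will lose more than 10 points of power.** This needs near-normal data, the median in every trial and a statistic that follows it. The plan itself calls for the mean when data look normal.
- **That the median is much less efficient in this setting.** This holds for normal data. With the asymmetric quartiles of section 7.1 the two are level, and with lognormal data the median is ahead.
- **That the switch protects nothing.** A permutation test does not need normality to be valid. But the choice of summary affects efficiency and interpretation when data are skewed or one team is very slow.
- **That the plan's type I error is 6–7%.** This is the result of deliberately keeping the better of two p-values, which the plan does not propose.
- **That the choice is made unblinded, or that the test statistic switches with the estimate.** The plan is silent on both. If the mean statistic were always used, the p-value would lose no power.

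None of this supplies the missing criterion, default or statistic. The boxplot rule is left to the eye, so it cannot be shown afterwards that the choice was made strictly on shape.

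**Conclusion.** The point holds as a gap in prespecification. The primary effect measure and its test statistic are undetermined until outcomes are available, and nothing elsewhere in the document settles them.

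The main measure of its size is the disagreement rate: in about 16% of trials at the planned effect, one analysis is significant and the other is not. That figure is nearly the same for normal data and for data matched to the cited quartiles, so it does not depend on the median being inefficient. The possible inflation of type I error is about 1 to 2 points, and only under best-of-two selection. Any loss of power depends on the data's shape and on how the choice is made, so it is not an expected cost of the plan.

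These figures assume 18 complete teams, the same shape in both arms, a pure shift and no site strata in the permutation. The Shapiro and outlier triggers are stand-ins for a visual judgement that the plan does not define.

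**What to change.** Before the data are unlocked, name one primary measure and use that same quantity for the estimate, the bootstrap interval and the permutation statistic. For example: *The primary effect measure is the difference in mean time to first epinephrine, whatever the distribution; the two-sided p-value comes from permuting this difference and the 95% interval from bootstrapping it.*

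The mean difference is suggested because section 7.1 is built on it. Fixing the median would close the gap equally well. Use boxplots for description only. Report the median difference with its bootstrap interval as a prespecified sensitivity analysis, and change checklist item 27d to match. Apply the same rule to the section 7.4.3 outcomes.

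The cost is a sentence or two in the SAP, with no new data or recruitment. The downside is that a mean is more sensitive to one very slow team and can be less powerful under marked skew (85.8% against 96.0% in the most skewed case above). The median sensitivity analysis would show this.

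### No bootstrap type is named for the 95% confidence intervals, and with 9 teams per arm the common types cover only about 91–92% for a mean difference

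*Combined protocol and SAP*

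**What the plan says.** Section 7.4.2 gives the small sample as its reason for non-parametric methods. Boxplots decide the estimand: the mean difference if the data look symmetric and normal, but "if the data are skewed or non-normally distributed, the median difference" is estimated instead. For the interval, "Bootstrapping with 10,000 resamples will be used to calculate 95% confidence" limits. Two-sided p-values come from a separate permutation test with 10,000 iterations.

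Section 7.4.3 applies the same approach to the remaining times, chest compression fraction and peri-shock pauses: "After assessing the data distribution, bootstrapping and permutation tests with 10,000" iterations supply intervals and p-values. Its template table has 9 teams per arm and prints the interval next to the p-value.

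Section 7.1 concludes that "18 teams (9 per arm) are required". Section 7.2 states: "Randomization will be conducted in a 1:1 ratio at the level of the team and stratified by study site". Sections 7.4.2 and 7.4.3 do not name a bootstrap type or a small-sample correction, and do not say whether resampling or permutation is done within site.

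**The concern.** The bootstrap is justified by large-sample theory, so a small sample is a weak reason to choose it. For a mean of 9 values, the resampling variance uses divisor 9 rather than 8, and the usual interval types make no allowance for the SD having been estimated. Both effects narrow the interval. For a median of 9 values, the bootstrap distribution is coarse, and the interval depends heavily on how its quantiles are used.

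What is at stake is the reported precision of the primary effect and of the section 7.4.3 results. Depending on a choice the SAP leaves open, an interval labelled 95% may be too narrow. Because the p-value comes from another procedure, interval and p-value can also disagree within one row of the results table.

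**Working it through.** **Inputs.** 9 teams per arm, SD 25.2 s in both arms and a 35 s effect (section 7.1); mean or median difference and 10,000 resamples (section 7.4.2). Coverage does not depend on the SD or on the size of a constant shift; 25.2 s serves only to express widths in seconds.

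**The plan's own figures.** The SD reproduces: (173 − 139)/1.35 = 25.2. The team number does not reproduce at two-sided 5% and 90% power: 2 × (25.2 × (1.960 + 1.282)/35)² = 10.9, or 11 per arm. That is a separate matter; this point needs only the planned 9 per arm.

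**Analytic check, mean difference, normal data.**

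- Bootstrap SE = √(8/9) × usual SE = 0.943 × usual SE.
- Multiplier on the usual SE: 1.96 × 0.943 = 1.848. The t interval with 16 df uses 2.120.
- Width ratio: 1.848/2.120 = 0.87, so about 13% narrower.
- Coverage: P(|t₁₆| ≤ 1.848) = 0.917. The miss rate is 8.3% instead of 5%, about 1.7 times the label.
- In seconds: usual SE = 25.2 × √(2/9) = 11.9. Full width is 2 × 1.848 × 11.88 = 43.9 s for the bootstrap and 2 × 2.120 × 11.88 = 50.4 s for t.

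**Simulated coverage (%).** 6,000 trials of 9 v 9, 2,000 resamples each, teams resampled within arm, no site effect. The Monte Carlo standard error near 91% is √(0.91 × 0.09/6,000) = 0.4 points.

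| Estimand, data | Percentile | Basic | Normal approx. | BCa | Studentized |
|---|---|---|---|---|---|
| Mean, normal | 91.3 | 91.4 | 91.6 | 91.3 | 95.2 |
| Mean, lognormal (σ 0.5) | 90.9 | 92.6 | 92.2 | 89.1 | 94.4 |
| Mean, exponential | 90.0 | 92.3 | 91.7 | 87.5 | 93.5 |
| Mean, lognormal (σ 1) | 89.2 | 94.2 | 93.1 | 84.6 | 92.9 |
| Median, normal | 96.9 | 84.8 | 95.3 | 95.2 | not run |
| Median, lognormal (σ 0.5) | 97.2 | 86.8 | 96.3 | 95.3 | not run |
| Median, exponential | 97.0 | 86.6 | 96.4 | 95.3 | not run |
| Median, lognormal (σ 1) | 97.0 | 89.8 | 97.2 | 95.1 | not run |

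With the planned 10,000 resamples (8,000 trials, normal data), percentile and basic coverage for the mean both stay at 91.3%. The shortfall comes from the 9 teams, not from the number of resamples.

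**Site effect.** The documents give none, so this is an assumption. Each arm is split 5/4 between sites and resampling ignores site. Percentile coverage for the mean (normal data) is then:

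- site difference 0.5 SD: 91.7%
- 1 SD: 94.1%
- 2 SD: 98.6%

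Ignored site variation widens the interval, while balanced allocation keeps it out of the arm comparison.

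**Disagreement between interval and p-value.** 3,000 trials per scenario, mean difference, normal data, no site effect, percentile interval (2,000 resamples), fully enumerated permutation test without site strata. The interval excluded zero while p > 0.05 in:

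- 3.7% of trials with no effect (interval excludes zero in 8.6%, permutation test rejects in 4.9%)
- 10.5% at 20 s
- 9.7% at 25 s
- 6.8% at the planned 35 s

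The opposite conflict did not occur.

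**The case against.** The strongest reply is that the plan does not commit to a poor interval. It says only that a bootstrap will be used, and a studentized bootstrap fits that wording and covers 95.2% for normal data. This stands. A reader might infer that the planned mean-difference interval simply is a 91% interval; the text does not support that, because the type is open. The defect is the open choice, and four of the five types checked fall short for the mean under normality.

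A reader might also take the median results as a general shortfall. They are a spread by type: percentile over-covers, BCa and the normal approximation are near or above 95%, and only the basic interval is low.

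Third, the skewed-data rows for the mean describe data that section 7.4.2 would send to the median. That is fair, so the conclusion rests on the normal row. Boxplots of 9 values will not sort perfectly, but coverage after that selection step was not simulated.

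Fourth, a real site difference would offset the shortfall if resampling ignores site. That is true at about 1 SD, but at 2 SD the interval over-covers. An offset that depends on an unknown quantity is not a reason to leave the method unspecified.

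Finally, one might infer that the primary test is compromised. It is not: the p-value comes from the permutation test, and the plan ties no decision rule to the interval. The conflicts are a reporting inconsistency in a minority of trials.

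**Conclusion.** The point holds as one of specification with a measurable consequence. At 9 teams per arm, percentile, basic, normal-approximation and BCa intervals for the mean difference cover about 91–92% and are about 13% narrower than a t interval. This assumes normal data, independent teams and no site effect. A studentized bootstrap reaches about 95% under the same assumptions. For the median difference, coverage is about 97% (percentile), 95% (BCa) or 85–90% (basic).

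No single unstudentized type suits both estimands: BCa works for the median but gives 91% for the mean under normality, and less under skew. With a percentile interval for the mean, interval and p-value would conflict in about 4% of null trials and 7% at 35 s. Type I error of the primary test is unaffected, so this should be settled before analysis but does not threaten the trial's main inference.

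**What to change.** State in section 7.4.2, before data are seen, one interval method for each planned estimand, and apply it to the section 7.4.3 outcomes. Two options fit the plan:

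1. **Keep the bootstrap:** studentized for mean differences, BCa for median differences.
2. **Invert the permutation test:** the 95% interval is the set of shifts not rejected at two-sided 5%, using the same statistic (mean or median difference) as the p-value. Interval and p-value then agree by construction. This assumes a constant shift between arms. A rank-based Hodges–Lehmann interval is not equivalent, because it targets neither of the plan's two estimands.

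Either way, specify that resampling or permutation is done within site, to match the stratified randomization; the plan does not currently say so for either procedure. One caution applies to option 1. The coverage figures above are for resampling within arm, ignoring site. With a 5/4 split, resampling within site draws from cells of 5 and 4 teams, where the SE shrinkage is √(4/5) = 0.89 and √(3/4) = 0.87 instead of 0.94. Coverage of the exact within-site procedure, especially for the median, should therefore be confirmed by a short simulation before the SAP is final. Option 2 avoids this difficulty.

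Cost: SAP wording and code, with no change to design, sample size or conduct. Mean-difference intervals become about 10–20% wider than percentile ones (1/0.87 = 1.15 for the t interval).
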